This is an adaptive design and parameters for formal sample size calculation in a new disease of a previously unknown virus are not available. Then the sample size and power analysis are indicative for review at each stage of adaptive design. In a standard two-arm, head-to-head trial, the sample size would have been as follows: in order to detect a difference in the laboratory-based primary outcome of 10% (assuming a 50% of participants receiving Hydroxychloroquine Phosphate/Sulfate turn test negative at day 7 and expected rates in comparator groups of 60%), at a significance level 5% and a power of 90%, a sample size of approximately 520 subjects in each group will be required. This sample size will be enough to detect a small-medium difference (Cohen’s d 0.3, a significance level 5% and a power of 90%) in the clinical primary outcome.

Trial Status

By July 03, 2020, the trial had recruited a total of about 470 participants across 12 centers after approval from National Bioethics Committee and Drug Regulatory Authority of Pakistan. Recruitment started on April 20, 2020. The recruitment is expected to continue for at least next three months subject to review of data monitoring and safety board as estimated in Version 1.7.

Trial Registration

Prospectively registered at **clinicaltrials.gov ID: NCT04338698**

*The full protocol is attached as an additional file, accessible from the Trials website (Final_1.7_Plain)*

*The study protocol has been reported in accordance with the Standard Protocol Items: Recommendations for Clinical Interventional Trials (SPIRIT) guidelines and this is a PDF version of protocol 1.7 without citations for specific sections nested at the top (SPIRIT_Nested,pdf)*

Key Words

SARS-CoV-2, Hydroxychloroquine, Azithromycin, Oseltamivir, multi-center, adaptive, randomization

Declarations

Authors declare no financial or any competing interests

Ethics Approval

The proposed study is approved by National Bioethics Committee of Pakistan **(notification attached)** and IRBs at majority of participating sites. Remaining sites have endorsed the ethics approval of both University of Health Sciences Lahore and National Bioethics Committee (NBC).

Certified that this trial has received ethical approval from the appropriate ethical committee as described above

Consent for publication

Applicable through this submission

Availability of data and materials

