***SPIRIT Guidance: Sample size***

*14 Estimated number of participants needed to achieve study objectives and how it was determined, including clinical and statistical assumptions supporting any sample size calculations*

This is an adaptive design and parameters for formal sample size calculation in a new disease of a previously unknown virus are not available. Then the sample size and power analysis are indicative for review at each stage of adaptive design. In a standard two-arm, head-to-head trial, the sample size would have been as follows: in order to detect a difference in the laboratory-based primary outcome of 10% (assuming a 50% of participants receiving Hydroxychloroquine Phosphate/Sulfate turn test negative at day 7 and expected rates in comparator groups of 60%), at a significance level 5% and a power of 90%, a sample size of approximately 520 subjects in each group will be required. This sample size will be enough to detect a small-medium difference (Cohen’s d 0.3, a significance level 5% and a power of 90%) in the clinical primary outcome. Additional considerations will need to make for the interim analysis at every stage of the adaptive design. Interim analysis will review sample size according to time to clearance also. Planned blinded sample size re-estimations will need to be undertaken in which we will constantly re-examine the original sample size assumptions. We will aim to maintain the trial power at 90% even if the original sample size assumptions turn out to be far from the observed data. The adaptation at each stage will allow us to drop out fewer promising interventions and will prevent an underpowered trial for the most promising interventions. As the planned modifications will be undertaken in a blinded fashion, there will be no increase in the type I error rate.

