***SPIRIT Guidance: Recruitment***

*15 Strategies for achieving adequate participant enrolment to reach target sample size*

All patients fulfilling the eligibility criteria and providing informed consent are eligible for this study. Going by the projections, it is expected to enroll substantial number of participants from clinical facilities. A coordination group has been created on digital platform for immediate response to queries, learning from each other’s experiences, and continuity of operations. However, if health system indicates creep, investigators could recruit patients self-isolating at homes. Upon identification by site investigators in the hospital, this cohort would be contacted by trained researchers and data collectors via phone and if informed consent is obtained, recruited. The allocated treatment medicines for 14 days would be delivered. Similarly, swab samples and other clinical information would be collected from participants’ homes in case they cannot travel for testing. All other clinical data would be collected via phone and entered directly into the IT module. The unused or used drug packaging will be collected from participants’ homes upon completion of recruitment period of testing negative on PCR whichever comes first. It is expected that a wider pool of both hospitalized and home-isolated patients would be enough to meet the estimated sample size within the given timeframe.

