***SPIRIT Guidance: Statistical methods***

*20a Statistical methods for analyzing primary and secondary outcomes. Reference to where other details of the statistical analysis plan can be found, if not in the protocol*

*20b Methods for any additional analyses (eg, subgroup and adjusted analyses)*

*20c Definition of analysis population relating to protocol non-adherence (eg, as randomized analysis), and any statistical methods to handle missing data (eg, multiple imputation)*

All trial data will be analyzed by biostatistician based at the University of Health Sciences, Lahore, using an a priori, approved analysis plan (SPSS 25.0). Interim analyses at each stage (first stage will be 10% of the total sample size) of the adaptive design will be pre-planned and undertaken confidentially keeping investigators and participants blind till the end of the trial. Primary and secondary outcomes will be analyzed in accordance to the group in which the participants were randomized deploying the intention-to-treat principle. The primary analysis will be expressed as odds ratio (OR) of the comparison between groups for the primary outcome. Interim analyses will be conducted without disclosing groups, thereby maintaining a level of blinding in interpretation of interim results. The confidential interim analyses at each stage of the adaptive design will examine for imbalance in co-morbidity at baseline. If any differences are observed then stratification may be modified confidentially. The results will be reported as point estimates and 95% confidence intervals. Secondary analysis will include in time-to-event data to directly compare the data among groups with survival plots and hazard ratios. This will permit evaluation of the decision to continue beyond Day 7 of treatment upon testing negative, potential drug effects besides informing valuable understanding of drug effectiveness. Stratified analyses will be done by baseline COVID-19 positive status upon testing and age groups. Multiple regression and Cox proportional hazards stratified analysis will be used to adjust for a small number of covariates taken from stratification factors if there were baseline imbalances. Secondary analyses will deploy multiple regression models as well Chi square, Fisher’s exact test and one-way ANOVA to compare groups. The two-sided p-value less than or equal to 0.05 will be taken as significant. Imputation method will be used to handle missing data.

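### A flat 0.05 rule across seven arms and two primary outcomes leaves family-wise error uncontrolled, and 520 per group gives 90% power only for one unadjusted comparison

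*Protocol*

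**What the plan says.** The Abstract names seven randomized groups and two primary outcomes on day 7: a negative PCR test (laboratory) and a two-point improvement on a seven-category scale (clinical). Under Statistical methods the primary analysis is an odds ratio for the comparison between groups. No reference group is named there, interim analyses are planned at each stage, and "The two-sided p-value less than or equal to 0.05 will be taken as significant".

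Under Sample size (and again in the Abstract) the only calculation is introduced with "In a standard two-arm, head-to-head trial, the sample size would have been as follows". It rests on "assuming a 50% of participants receiving Hydroxychloroquine Phosphate/Sulfate turn test negative at day 7 and expected rates in comparator groups of 60" per cent, and concludes that "at a significance level 5% and a power of 90%, a sample size of approximately 520 subjects in each group will be required". The same number is said to suffice for the clinical outcome at Cohen's d of 0.3. The section calls these figures indicative, says interim analyses need further consideration, allows arms to be dropped, and states: "We will aim to maintain the trial power at 90% even if the original sample size assumptions turn out to be far from the observed" [...]. It closes by asserting that type I error will not increase, and the only reason given is that modifications are made blind.

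On accrual, the Abstract's Trial Status reports that by 3 July 2020 "the trial had recruited a total of about 470 participants across 12 centers". Recruitment began on 20 April and is expected to run at least three more months. The Recruitment section expects that a wider pool of hospitalized and home-isolated patients "would be enough to meet the estimated sample size within the given timeframe".

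**The concern.** The calculation covers one pairwise test at one look. The trial can produce six comparisons with hydroxychloroquine (the reference implied by the sample size assumption) or 21 pairwise comparisons, on each of two primary outcomes, and the one stated threshold is 0.05. The protocol then gives an assurance about type I error whose reason does not address this. Blinded re-estimation of nuisance parameters leaves the error rate of a single test essentially intact. It does nothing about the number of tests. Dropping less promising arms also needs between-arm results, even if the arms are only coded.

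Two misreadings are at stake. One regimen could be declared better at a family-wise error several times the nominal 5%. A null result on the laboratory outcome could be read as 90% powered within a plan that controls error, when it would not be.

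**Working it through.** **Inputs.** From Sample size: 50% v 60%, 5%, 90%, 520 per group, d = 0.3. From Statistical methods: two-sided 0.05. From the Abstract: seven arms, two primary outcomes, about 470 recruited between 20 April and 3 July 2020 (74 days), at least three more months. Assumed: equal allocation, which fits the block sizes of 28 and 42 for seven treatments.

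**1. The protocol's own figure.** With pooled variance and no continuity correction,

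n = [1.96 × √(2 × 0.55 × 0.45) + 1.2816 × √(0.25 + 0.24)]² / 0.10² = (1.379 + 0.897)² / 0.01 ≈ 518, rounded up to 519.

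Power at 520 is Φ[(0.10 × √520 − 1.96 × 0.7036) / 0.70] = Φ(1.288) = 90.1%. The 520 therefore reproduces for one unadjusted comparison.

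**2. Family-wise error when all arms are equal and every test uses 0.05.** Seven independent standard normal arm means were simulated 400,000 times, with z = (Xi − Xj)/√2 and rejection at |z| > 1.96. The two-outcome column counts a false positive on either outcome, with an assumed correlation between outcomes from 0.8 (lower figure) to 0 (higher figure).

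| Comparisons | One outcome | Two outcomes, either suffices |
|---|---|---|
| 6 v hydroxychloroquine | 20.7% | 30-37% |
| All 21 pairs | 44.0% | 59-69% |

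Interim looks are not included.

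**3. Power at 520 per arm once alpha is controlled.** For the laboratory outcome the formula in step 1 is used with the adjusted critical value c in place of 1.96. For example, Dunnett over six has c = 2.563, so power = Φ[(2.280 − 2.563 × 0.7036) / 0.70] = Φ(0.68) = 75%. For the clinical outcome, power = Φ(0.3 × √(520/2) − c) = Φ(4.837 − c).

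| Control | Two-sided alpha per test | Laboratory power | n per arm for 90% (laboratory) | Clinical power, d = 0.3 |
|---|---|---|---|---|
| None | 0.05 | 90.1% | 519 | 99.8% |
| Dunnett, 6 | 0.0104 | 75.2% | about 730 | not run; lies between the rows above and below |
| Bonferroni, 12 (6 × 2 outcomes) | 0.00417 | 64.7% | 849 | 97.6% |
| Bonferroni, 42 (21 × 2 outcomes) | 0.00119 | 50.0% | 1,010 | 94.5% |

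**4. Accrual (secondary).** 470/74 = 6.35 per day. Another 91 days gives 470 + 91 × 6.35 ≈ 1,048 patients, or about 150 per arm over seven equal arms. Seven arms of 520 would be 7 × 520 = 3,640, which needs (3,640 − 470)/6.35 ≈ 499 further days. If recruitment were cut at once to two arms, each would reach 470/7 + 578/2 = 67 + 289 = 356.

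**The case against.** The protocol is open about the two-arm basis. It calls the sample size indicative, promises re-estimation and arm dropping, and nowhere claims 90% power for a family of seven-arm tests. It cites an a priori analysis plan, not at hand, where comparison families and adjustment would normally sit. The 0.05 sentence directly follows a list of secondary tests, so it may not have been written with the primary analysis in mind. No section says that 12 or 42 tests will be run. The objectives join the two outcomes with *and*; if both were required for success, the second would add no inflation.

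Much of this stands, and it rules out several stronger readings.

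- A reader might infer that the 5% error rate and the 90% power both fail as written. They do not. At the protocol's own unadjusted 0.05, the 90% is right for each comparison and only the family-wise error fails. Power falls only once alpha is controlled.
- A reader might infer that both primary outcomes lose power. At d = 0.3 the clinical outcome loses little. (Cohen's d does not match a binary two-point improvement; that is a separate matter.)
- A reader might call a false positive likely. It exceeds one half only for all pairs on both outcomes with either sufficing.
- A reader might take the accrual figures as proof of failure. They are a projection from a constant rate to a stated minimum period, and the Recruitment section counts on a wider pool.

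The objection does not remove the core. The 0.05 sentence carries no exception for the primary outcomes, and the type I error assurance is a positive statement with a reason that does not support it. An unseen plan that adjusted alpha would conflict with that sentence and would change the meaning of 520 and 90%.

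**Conclusion.** The point holds. The stated threshold and the stated assurance do not control error over seven arms and two primary outcomes. On one outcome, family-wise error is about four times nominal for six comparisons with hydroxychloroquine (21%) and about nine times for all pairs (44%). The two-outcome figures apply only if either outcome suffices. All assume equal regimens, every test at 0.05 and no interim looks.

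On the laboratory outcome, 520 per arm cannot give both family-wise control and 90% power: power is 75%, 65% or 50%, depending on the family and method. The shortfall against stated accrual is a lesser, conditional point. It assumes a constant rate, equal arms and exactly three more months. Even so, the two-arm figure of about 356 shows that arm dropping alone would not reach 520 in that period.

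**What to change.** - Under Statistical methods, replace the flat rule with a named, small primary family, for example six comparisons with hydroxychloroquine. State whether success needs one or both primary outcomes. Control alpha over the family with Dunnett or Holm. If either outcome suffices, split alpha across the two or order them; the order is the sponsor's choice, since the protocol gives both primary status. Report all other pairs as estimates with confidence intervals.
- Under Sample size and in the Abstract, say that 90% is per comparison and unadjusted, and that laboratory-outcome power at 520 per arm is about 75% after Dunnett over six. If alpha is shared over both outcomes by Bonferroni over 12, the figure is about 65%.
- Limit the type I error assurance to blinded sample size re-estimation.
- Reconcile the Recruitment statement with Trial Status by giving the target, the number of arms it applies to and the period. The projection above is a reason to do this and should not be written into the protocol as fact.

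The cost is wording in the protocol and analysis plan and a less favourable power statement. No patients are added, so the lower laboratory-outcome power would be accepted. Keeping 90% there would need about 730 per arm under Dunnett over six.

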**8 DATA SAFETY AND MONITORING**

The independent National Data Safety and Monitoring Board (NDSMB) has been notified by Drug Regulatory Authority of Pakistan to oversee all Covid-19 research **(Annex II).** It comprises eminent physicians, researchers, biostatisticians and officials that will scrutinize data for compliance with given patient safety standards as per Good Clinical Practices. It’s also vested with authority to decide on halting a study or an intervention arm until a subsequent review is conducted. It is supervised by the Chairman and each of the meeting is recorded by the designated Secretary.

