***SPIRIT Guidance: Data monitoring***

*21b Description of any interim analyses and stopping guidelines, including who will have access to these interim results and make the final decision to terminate the trial*

In line with well-established editorial standards, the interim analyses will be done independently of the authors of the paper and investigators. To achieve that, NDSMB will establish an interim analysis sub-committee of independent individuals who will be named in acknowledgment section of the paper. The study statistician will be part of this committee and will give a written undertaking to keep that interim findings blind from the clinical investigators. The NDSMB meeting agenda will have an open and a closed part, the latter part will only by attended by interim analysis sub-committee. All decisions including termination of the study and related observations will be communicated to the investigators in writing by the Secretary of NDSMB.

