***SPIRIT Guidance: Dissemination policy***

*31a Plans for investigators and sponsor to communicate trial results to participants, healthcare professionals, the public, and other relevant groups (eg, via publication, reporting in results databases, or other data sharing arrangements), including any publication restrictions*

Subsequent to NDSMB review and approval, findings of interim analysis and relevant results are to be announced publicly and submitted for publication in a scientific journal for dissemination to the scientific community and public at large represented by the study participants.

*31b Authorship eligibility guidelines and any intended use of professional writers*

The final manuscript would be published as group authorship with investigators’ names mentioned in acknowledgement section in alphabetical order.

*31c Plans, if any, for granting public access to the full protocol, participant level dataset, and statistical code*

If NDSMB permits, any part or whole of the protocol, site-specific data, or the entire dataset could be made available to public for academic use only.

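### The 0.05 significance rule is not limited to the final analysis although arms are compared at every stage; if interim results may be claimed at that level, the error per comparison exceeds 5%

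*Protocol*

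**What the plan says.** Under Statistical methods (SPIRIT items 20a to 20c) the protocol states: "Interim analyses at each stage (first stage will be 10% of the total sample size) of the adaptive design will be pre-planned". The same section gives the only significance criterion in the document: "The two-sided p-value less than or equal to 0.05 will be taken as significant". Results are to be reported with ordinary 95% confidence intervals. The section also says that interim analyses are confidential, with investigators and participants kept blind until the trial ends, and that groups are not disclosed in them.

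Under Sample size (item 14) the looks are given a comparative use: "The adaptation at each stage will allow us to drop out fewer promising interventions". That section concedes "Additional considerations will need to make for the interim analysis at every stage of the adaptive design", but closes by asserting that the type I error rate does not rise because the planned modifications are made blind.

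The looks have consequences. The monitoring board is "vested with authority to decide on halting a study or an intervention arm until a subsequent review is conducted" (section 8, Data Safety and Monitoring). Under Data monitoring (item 21b), "All decisions including termination of the study and related observations will be communicated to the investigators in writing". Under Dissemination policy (item 31a), after board review and approval, "findings of interim analysis and relevant results are to be announced publicly and submitted for publication in a scientific journal".

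**The concern.** Read together, these sections allow comparisons between arms at every stage, one unqualified threshold, decisions that include termination, and publication of interim findings. Nothing in the protocol prevents an interim p of 0.05 or less from being presented as a significant effect. If that happens, the same null hypothesis gets a fresh chance of false rejection at each look. This would arise with two arms and one outcome, so it is separate from multiplicity over seven arms and two primary outcomes.

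The assurance about type I error makes it more than a missing detail. A reader of the protocol is told that the question is settled, on grounds that cover only one of the planned adaptations. At stake is whether the 5% level used for the sample size is the level at which the trial makes its claims, above all for a claim from an early, small look.

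**Working it through.** **Inputs from the protocol.** Two-sided level 0.05; first look at information fraction 0.10; a look at every stage (Statistical methods). Rates of 50% v 60%, power 90%, about 520 per group (Sample size).

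**Assumptions.** The number and timing of later looks are not stated; I take 2 to 10 looks including the final one, the first at 10%. Allocation is taken as equal, and figures are per pairwise comparison.

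**1. The stated sample size.** With pooled variance, two-sided and without continuity correction:

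n = [1.960·√(2·0.55·0.45) + 1.282·√(0.5·0.5 + 0.6·0.4)]² / 0.10² ≈ 518.04, rounded up to 519.

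This reproduces the stated 520, at which power is 90.1%. So 520 is the figure for a single test at 0.05, with no allowance for interim tests.

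**2. Error if every look is judged at 0.05.** Under no true difference, the statistics Z₁,…,Z_K at fractions t₁<…<t_K=1 are standard normal with corr(Z_j, Z_k) = √(t_j/t_k) for j<k. The error is P(|Z_k| ≥ 1.96 for at least one k). Numerical integration over the independent increments gives:

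| Looks at (% of sample) | Error per comparison |
|---|---|
| 100 only | 5.0% |
| 10, 100 | 9.5% |
| 10, 50, 100 | 12.3% |
| 10, 40, 70, 100 | 14.0% |
| 10, then four evenly spaced to 100 | 15.4% |
| 10, 25, 50, 75, 100 | 15.8% |
| every 10 | 19.3% |

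Simulation agrees to within about 0.15 percentage points.

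**3. Does hiding the labels help?** Swapping the labels of two groups turns Z into −Z. |Z| and the two-sided p-value do not change, so the table is the same with coded groups. Blinded sample size re-estimation is different: it uses pooled data and makes no comparison between arms, so the protocol's assurance can hold there.

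**4. Error with an interim boundary.** Take p<0.001 at each interim look (Haybittle-Peto).

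- Final level left at 0.05: 5.1% with two looks and 5.2% with ten, slightly over.
- Final level 0.047: with two looks the error cannot exceed 0.001 + 0.047 = 0.048. With ten looks the integration gives 4.9%.

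With an O'Brien-Fleming shape, the final-look level that holds 5% overall is 0.050 (10/100), 0.048 (10/50/100), 0.043 (10/25/50/75/100) and 0.037 (every 10%).

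**5. Cost in power.** The standard errors at 520 per group are √(2·0.55·0.45/520) = 0.03085 under the null and √(0.49/520) = 0.03070 under the alternative. Power of the final test is Φ[(0.10 − z·0.03085)/0.03070]. With z = 1.960 this is 90.1%; with z = 1.986 (level 0.047) it is 89.6%.

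**The case against.** The strongest reply is that the protocol does not fix the procedure tabulated above. The 0.05 sentence follows the description of secondary analyses and is not stated for interim looks. The purposes given for the looks are sample size review, dropping weaker arms and checking baseline balance; none is an early claim of benefit. The termination text names no ground, and the board's described task is to check data against patient safety standards; stopping for safety or futility does not raise the false-positive rate for benefit. Interim results are said to stay confidential until the trial ends, and boundaries may stand in the approved analysis plan, which is not at hand.

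Much of this stands. A reader might infer that an interim p of 0.05 or less stops the trial for benefit, or that the false-positive rate is 10% to 19% as a matter of fact. The documents support neither: no such rule is written, and the number of looks is unknown.

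Three things remain. The threshold is unqualified and is the only one given. The confidentiality text and the plan to announce interim findings are not reconciled; release only at the end is a possible reading, but the protocol does not say so. And the assurance about type I error is too broad as worded. A boundary in the analysis plan would control the error, but the protocol's flat 0.05 would then contradict that plan and would still need correcting.

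**Conclusion.** The concern holds in conditional form. The protocol sets one significance level without confining it to the final analysis, provides for comparisons between arms at each stage that may lead to termination or publication, and gives an assurance about type I error that is valid only for blinded sample size re-estimation.

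The size depends on how the looks are used. If the formal test is made only at the end, repeated looks for benefit add nothing and the error per comparison is 5%. If any look may be claimed as significant at 0.05, it is 9.5% with one interim look at 10% and 19.3% with ten equal looks; more looks would exceed that. These figures rest on the assumed 2 to 10 looks and leave out multiplicity over arms and outcomes. The matter should be corrected; the protocol does not show that inflation will in fact occur.

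**What to change.** - **Statistical methods:** limit the 0.05 rule to the final analysis. State that no claim of benefit, termination for benefit or published statement of significance is made at an interim look unless a pre-specified boundary is crossed. One option is two-sided p<0.001 at interims with a final level of about 0.047, which keeps the overall error per comparison at or below 5% for up to ten looks. Another is an O'Brien-Fleming-type spending function. If the analysis plan already sets a boundary, cite it in place of the flat 0.05.
- **Data monitoring and Dissemination policy:** refer to that boundary, and say when interim findings may be released, so that the text agrees with the confidentiality statement under Statistical methods.
- **Sample size:** restrict the statement that type I error does not increase to blinded sample size re-estimation.

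Safety halts are unaffected. The cost is a few sentences and no extra participants. The downside is about half a percentage point of final power at 520 per group under the p<0.001 and 0.047 option (90.1% to 89.6%) and a stricter bar for an early claim.
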